## Abstract

**Background:**

Myocardial damage in patients undergoing cardiac surgery increases both morbidity and mortality. Different protective strategies dealing with either preconditioning or postconditioning or assessing a single aspect of cardioprotection have shown conflicting results. We tested the hypothesis that a multimodal approach would improve cardioprotection and limit myocardial damage following cardiac surgery with cardiopulmonary bypass.

**Methods:**

This study is a pragmatic multicenter (six French institutions), prospective, randomized, single-blinded, controlled trial. The randomization is stratified by centers. In the study, 210 patients scheduled for aortic valve surgery with or without coronary artery bypass grafting will be assigned to a control or a treatment group (105 patients in each group). In the control group, patients receive total intravenous anesthesia with propofol and liberal intraoperative blood glucose management (initiation of insulin infusion when blood glucose, measured every 60 min, is greater than 180 mg/dl), as a standard of care. The treatment group receives a bundle of care combining five techniques of cardioprotection: (1) remote ischemic preconditioning applied before aortic cross-clamping; (2) maintenance of anesthesia with sevoflurane; (3) tight intraoperative blood glucose management (initiation of insulin infusion when blood glucose, measured every 30 min, is greater than 140 mg/dl); (4) moderate respiratory acidosis (pH 7.30) at the end of cardiopulmonary bypass; and (5) a gentle reperfusion protocol following aortic unclamping. The primary outcome is myocardial damage measured by postoperative 72-h area under the curve of high-sensitivity cardiac troponin I.

**Discussion:**

The ProCCard study will be the first multicenter randomized controlled trial aiming to assess the role of a bundle of care combining several cardioprotective strategies to reduce myocardial damage in patients undergoing cardiac surgery with cardiopulmonary bypass.

**Trial registration:**

ClinicalTrials.gov, NCT03230136. Registered on July 26, 2017. Last updated on April 17, 2019.

**Electronic supplementary material:**

The online version of this article (10.1186/s13063-019-3638-3) contains supplementary material, which is available to authorized users.

## Background

Cardiac surgery with cardiopulmonary bypass (CPB) induces, consecutive to aortic clamping–unclamping, myocardial damage related to ischemia-reperfusion. The most common myocardial protection technique involves administration of a cardioplegic solute into the coronary arteries. Nevertheless, elevated postoperative cardiac troponin release remains a marker of poor prognosis after cardiac surgery [1, 2]. Many studies have, therefore, attempted to reduce myocardial ischemia-reperfusion injuries during CPB.

The protective effect of ischemic preconditioning was first described in 1986 by Murry et al. [3]. This process involves applying transient brief episodes of ischemia before subsequently sustained ischemia to render the myocardium more resistant to an ischemic insult. More recently, similar interventions applied at the onset of reperfusion, a process named postconditioning by analogy with preconditioning, have been described [4]. Since these first publications, a very large number of experimental studies have been carried out to characterize these phenomena and to understand their mechanisms. In a second stage, several clinical studies have attempted to reproduce these results in humans, with rather mixed results [5]. Most studies have been done in patients undergoing CPB. However, these specific clinical conditions, such as the major inflammatory processes induced by the heart–lung machine, the influence of the anesthetic agents, or the specificity of each cardiac surgical procedure, may complicate the interpretation of the results of such studies. Moreover, all the clinical studies that have been done to date have tested a single factor of myocardial protection, such as the administration of cyclosporine, the beneficial effects of anesthesia by means of halogenated volatile anesthetics, or the effect of remote ischemic preconditioning (RIPC) [6–8]. The biological effect of a single cardioprotective procedure might not be strong enough for translation into heterogeneous routine clinical situations, conversely to standardized experimental models.

The combination of multiple cardioprotective procedures offers the potential for increasing the biological and clinical effects of cardioprotection. Experimental work has found a synergistic effect of cardioprotection. However, no clinical study has sought to combine the beneficial effects of several techniques of cardioprotection in patients undergoing heart surgery with CPB [9, 10].

The present study evaluates the effect of a bundle of care combining several cardioprotective techniques during cardiac surgery. We seek to evaluate the effect and feasibility of adding different simple and patient-safe procedures compared to standard of care to reduce myocardial damage in patients undergoing CPB.

## Methods/design

### Design

ProCCard is a multicenter, prospective, randomized, controlled, single-blinded, two-arm study comparing a bundle of care combining five techniques of cardioprotection to a conventional approach in cardiac surgery with CPB. The trial is performed in accordance with the declaration of Helsinki (revised version, 2013), the European Guidelines for Good Clinical Practice (revised version, 2016), and the French laws. A checklist of recommended items to address in a clinical trial protocol according to the "Standard Protocol Items: Recommendations for Interventional Trials (SPIRIT 2013 Checklist)" is provided in Additional file 1. 

### Study population

#### Screening and inclusion

Patients are screened during the preoperative visit by the anesthesiologist, informed, and included after providing written consent.

#### Inclusion criteria

Patients scheduled for aortic valve surgery, with or without coronary artery bypass, older than 18 years, are eligible for enrollment.

#### Exclusion criteria

Emergency surgeryRedo surgeryPreoperative treatment with nicorandil (an adenosine triphosphate-sensitive potassium channel opener), sulfonylurea, or repaglinide (two adenosine triphosphate-sensitive potassium channel blockers)Preoperative acute circulatory insufficiency justifying catecholamine support or mechanical circulatory assistanceSevere chronic renal insufficiency (glomerular filtration rate < 30 ml/min)Severe chronic liver disease (spontaneous international normalized ratio > 2),Severe respiratory insufficiency (forced expiratory volume in 1 s < 40% theoretical value)Acute coronary syndrome less than 7 days oldCurrent infectionPeripheral arterial disease at upper limbsAny other surgical procedure associated with aortic valve surgery (combined valve surgery, Morrow’s myotomy, etc.)

### Perioperative procedure

Standard intraoperative monitoring consists of a five-lead electrocardiogram, frontal electroencephalography (BIS-monitor A2000®; Aspect Medical Systems, Norwood, MA, USA), pulse oximetry, peripheral arterial catheter, central pressure monitoring, capnography and vesical temperature probe.

Intravenous anesthesia is induced with either etomidate or propofol, sufentanil, or remifentanil (at the discretion of the investigator), and cisatracurium. The maintenance of anesthesia depends on the experimental group assignation. After systemic heparinization (300 IU/kg, activated clotting time > 400 s), the ascending aorta and right atrium are cannulated. A standard CPB with a disposable hollow-fiber membrane oxygenator is started with a target output of 2.4 l/min/m^2^ of body surface area. Surgery is performed under mild hypothermia (> 35 °C). After aortic cross-clamping, cardioplegia is achieved with crystalloid or blood solution, according to local protocols. After aortic unclamping, the heart is defibrillated if sinus rhythm does not resume spontaneously. Patients are transferred to the intensive care unit (ICU) and extubated when pressure support ventilation is tolerated.

### Experimental protocol

#### Randomization

Written informed consent is obtained for all patients before inclusion. Patients are randomly assigned to either the intervention or control group. Computer-generated randomized lists are drawn up by the Biostatistics Department of the Hospices Civils de Lyon before the start of the study. The randomization is stratified by i) centers and ii) individual need to perform coronary bypass during aortic valve surgery. The allocation is implemented in the electronic case report form.

#### Treatment group

In the treatment group, patients receive a bundle of care combining five techniques of cardioprotection (Table 2):
After intravenous induction, anesthesia is maintained during surgery with sevoflurane to induce both preconditioning and postconditioning. During CPB, sevoflurane is administered through the heart–lung machine only in two institutions (Lyon University Hospital and Arnault Tzanck Institute). In the four remaining centers, because the device for administering sevoflurane is not available on the heart–lung machine, propofol is administered during CPB.RIPC is applied using a Riester® pneumatic tourniquet placed on the upper arm (Riester Company, 72,417 Jungingen, Germany). Three cycles of 5-min inflation to 200 mmHg/5 min deflation are performed after anesthesia induction and before skin incision.Intraoperative blood glucose management involves the initiation of insulin infusion when blood glucose, measured every 30 min, is greater than 140 mg/dl.During CPB, 5 min before aortic unclamping, blood gases are adjusted by limiting the flow of air/oxygen mixture in the heart–lung machine, in order to obtain an arterial blood pH lower than or equal to 7.30, and consequently to limit the “pH paradox” phenomenon occurring at the time of reperfusion [11, 12].Just after aortic unclamping, a “gentle reperfusion” protocol is applied, consisting of a gradual recovery of the CPB flow (initial recovery of the flow at 20% of the theoretical flow, with an increase of 20% every 30 s, until a complete restoration of the CPB flow in 2 min) to limit reperfusion injuries.

**Table 2 Tab2:** Perioperative protocol in each of the two treatment arms

	Control group	Treated group
Maintenance of anesthesia	Propofol	Sevoflurane
RIPC	No	Three cycles of: 5 min inflation to 200 mmHg/5 min deflation
Intraoperative blood glucose (BG) management	BG control every 60 min. Intravenous insulin infusion if BG greater than 180 mg/ml	BG control every 30 min. Intravenous insulin infusion if BG greater than 140 mg/ml
pH level at the end of CPB, before aortic unclamping	pH ≥ 7.40	pH ≤ 7.30
Gentle reperfusion	No	Gradual recovery of the CPB flow (initial recovery of the flow at 20% of the theoretical flow, with an increase of 20% every 30 s, until complete restoration in 2 min)

#### Control group

In the control group, patients are managed according to a standard of care (Table 2):
Anesthesia is maintained with continuous infusion of propofol during surgery (halogenated volatile anesthetics are not allowed in this group).Intraoperative blood glucose management involves the initiation of insulin infusion when blood glucose, measured every 60 min, is greater than 180 mg/dl.During CPB, 5 min before aortic unclamping, blood gases are adjusted by modifying the flow of air/oxygen mixture on the heart–lung machine to obtain an arterial blood pH higher than or equal to 7.40.Just after aortic unclamping, the theoretical CPB flow is restored at the earliest, according to the clinical tolerance of the patient (no gentle reperfusion).

### Outcomes

The primary outcome is the postoperative 72-h area under the curve (AUC) for high-sensitivity cardiac troponin I (hsTnI) release. Blood samples are collected after induction of anesthesia (baseline) and 4, 8, 12, 24, 48, and 72 h after aortic unclamping (Table 3). All samples are frozen carefully and sent to a centralized laboratory for measurement (see below).

**Table 3 Tab3:** ProCCard trial schedule during the study period

	Preoperative day	Day of surgery				Postoperative day	Hospital discharge	Postoperative day
		Baseline	Before aortic unclamping	ICU arrival	H4-H8-H12	H24-H48-H72		Day 30
Eligibility screen	x							
Informed consent	x							
Randomization		x						
High-sensitivity troponin I		x			x	x		
Blood glucose level		x	x	x				
Arterial lactate		x		x	x (H8)			
Arterial pH			x	x				
Creatininemia	x			x		x		
ECG	x			x		x		
Trans-thoracic echocardiography	x						x	
Quality of life	x							x
Visit before hospital discharge							x	
Phone call								x
Adverse events		x	x	x	x	x	x	x

The secondary outcomes are hsTnI level (peak and 24 h after aortic unclamping), extubation time, length of stay in ICU and hospital, Index Gravity Score (IGS II; the scoring system measuring the severity of disease for patients admitted to ICU), the three-level version of EQ-5D (EQ-5D-3 L) health status score (comparison between preoperative and 30 day postoperative), and the need for catecholaminergic support [13]. Major adverse events occurring during 30 postoperative days are collected and reported as follows: all-cause of death, serious infection requiring antibiotic therapy, major bleeding requiring transfusion of ≥ 5 U packed red blood cells or surgical intervention, respiratory insufficiency, stroke, arrhythmia requiring medical therapy.

### Data collection

#### Baseline data

The following data are collected in the preoperative period: initial valvular aortic pathology requiring surgical correction, concomitant pathology (hypertension, dyslipidemia, diabetes, stroke, atrial fibrillation, chronic obstructive pulmonary disease, smoking), and medications (β-blockers, nitrates, statins, Ca^2+^ channel blockers, angiotensin-converting enzyme inhibitor, angiotensin II receptor blocker, diuretics, platelet inhibitors, insulin, oral antidiabetic drugs, amiodarone, heparin, oral anticoagulant therapy), age, sex, body mass index, NYHA class, ASA class, Logistic EuroSCORE I, blood creatinine level, blood hemoglobin level, electrocardiogram, EQ-5D-3 L health status score, echocardiography (left ventricular (LV) ejection fraction, LV mass index calculated using LV end-diastolic diameter, LV end-diastolic posterior wall thickness, LV end-diastolic interventricular wall thickness).

#### Intraoperative data

During surgery, the following data are collected: CPB duration (min), aortic cross-clamping duration (min), type and volume of cardioplegia (ml), surgical procedure performed, baseline hsTnI level, baseline lactate level, total IV sufentanil/remifentanil (μg), total IV propofol (mg), total IV insulin (IU), catecholaminergic treatment, blood glucose concentrations during the operative period, arterial blood gas harvested 5 min before aortic unclamping.

#### Postoperative data

The following data are also collected (Table 3): blood lactate (ICU arrival, and 8 h after aortic unclamping) and creatinine (ICU arrival, 24, 48, and 72 h after aortic unclamping) levels, electrocardiogram (ICU arrival, 24, 48, and 72 h after aortic unclamping), extubation time, SAPS II, length of stay in ICU and hospital, echocardiography at 5-day postoperative (LV ejection fraction, LV mass index), EQ-5D-3 L health status score at 30 day postoperative (phone call), any adverse event occurring during this period.

#### Centralized analysis of hsTnI

Blood samples for the analysis of hsTnI are collected in each institution, centrifuged at 2000 g for 10 min. The supernatant is removed and stored in a freezer (− 80 °C) before transfer for centralized analysis to the Biochemical Laboratory at the Lyon University Hospital (ARCHITECT STAT Troponin I; Abbott, North Chicago, IL, USA).

#### Sample size

The sample size calculation was performed according to hypotheses stemming from a previous study carried out in the department of cardiac anesthesia of the same facility [6]. One hundred patients per arm would ensure an 80% power of detecting a decrease in the AUC of hsTnI release within the three first postoperative days (AUC of 242 in the control arm and 169 in the treatment arm) considering a common standard deviation of 183 and a two-sided Student test. Assuming a 5% rate of missing data, there should be 105 patients in each arm; thus, 210 patients are to be included in the study.

#### Statistical analyses

The main analysis will be carried out within the intention-to-treat (ITT) population. The ITT population is defined as all patients included in the study whatever the selection criteria, the treatment strategy, or the adequacy for evaluation. All missing data necessary for the calculation of the outcome criterion (AUC of serum level of hsTnI within 3 days after surgery) will be imputed. The causes and contexts of missingness will orient the choice of the imputation method. The main analysis will compare the AUC of serum level of hsTnI within 3 days after surgery between the treatment and the control arm using a mixed-effect generalized linear model. According to the recommendations of the international conference on harmonization of technical requirements for the registration of pharmaceuticals for human use (ICH), each variable used for the stratification of the randomization will be introduced in the model as a random effect or fixed effect. Variable “arm” will be introduced as a fixed effect. Statistical significance on two-sided Wald test will be set at 0.05.

The same analysis will be carried out on the per-protocol (PP) population. The PP population is defined as all patients of the ITT population with no major deviation from the study protocol. This analysis will consider the actually applied strategy. A sensitivity analysis will be carried out after excluding all patients who experienced, within 3 days after surgery, any event able to bias the analysis of the main outcome. The main outcome will also be analyzed using a mixed-effect generalized linear model to investigate the effect of patient management through considering various practices likely to influence hsTnl kinetics, especially glycemic and lactic acidosis monitoring.

All secondary outcomes will be summarized, per arm, according to their nature (qualitative or quantitative). The peak of serum level of hsTnI and the level of hsTnI at 24 h after aortic unclamping will be analyzed in the same way as the main outcome. The duration of mechanical ventilation and the duration of stay in the ICU will be similarly analyzed either after log-transformation of the values or using a survival analysis technique (time-to-event analysis of the time to mechanical ventilation discontinuation or the time to discharge from hospital, respectively). A frailty Cox model may be used to allow for the variables used for stratification. The length of hospital stay will be analyzed with a Cox frailty model adjusted for the variables used for stratification. The IGS II will be analyzed in the same way as the main outcome after checking the score distribution. If necessary, an adequate score transformation may be applied.

The need for catecholaminergic support will be analyzed with a logistic model adjusted for the variables used for stratification.

The occurrence of at least one postoperative complication will be analyzed with a logistic model adjusted for the variables used for stratification. The complications considered are: post-operative hemorrhage, need for postoperative blood transfusion, the need for revision surgery for bleeding, the occurrence of respiratory insufficiency requiring intubation or not, postoperative infection, neurological disorder, and complete arrhythmia by atrial fibrillation. The postoperative adverse events will be analyzed in the safety population. The safety population is defined as all patients of the ITT population who received any treatment of the actually applied strategy. The proportions of patients concerned by the secondary outcomes will be calculated by arm and type of complication.

The EQ-5D-3 L score will be analyzed using a mixed linear regression model that will include a variable for “time” (at 30 days after surgery vs before surgery), a variable for “group”, and an interaction between these two variables. This model will also be adjusted for the variables used for stratification. The coefficient of interaction will be tested to compare the arms. The score distribution will be examined for floor and/or ceiling effects. If necessary, a Tobit model will be used. Survival will be analyzed with a Cox model adjusted for the variables used for stratification.

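### Naming baseline hsTnI as a covariate in the primary model would be a free gain in precision; the model as written is valid and meets its stated power

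*Protocol article*

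**What the plan says.** The Statistical analyses section compares the AUC between arms with a mixed-effect generalised linear model. Arm "will be introduced as a fixed effect", and "each variable used for the stratification of the randomization will be introduced in the model as a random effect or fixed effect". No other term is named for the main analysis. Peak and 24-hour hsTnI are to be handled in the same way as the main outcome, so they inherit the same terms.

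The baseline value is part of the trial's data. Outcomes: "Blood samples are collected after induction of anesthesia (baseline) and 4, 8, 12, 24, 48, and 72 h after aortic unclamping", with all samples sent to one laboratory. The Intraoperative data list includes "baseline hsTnI level, baseline lactate level". The section on centralised hsTnI analysis describes processing, storage and the single assay.

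The model's covariates are defined by reference to the stratification factors, and the article gives those in two forms. The abstract says "The randomization is stratified by centers" and mentions no other factor. The Randomization section says "The randomization is stratified by i) centers and ii) individual need to perform coronary bypass during aortic valve surgery".

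**The concern.** When an outcome is also measured before treatment, its baseline value is often among the better predictors of the later value. Adjusting for it removes outcome variance that has nothing to do with treatment, and corrects the estimate for chance differences between arms at baseline. The plan already draws on a preoperative value for EQ-5D-3L, through a time-by-group model, but names no such term for the primary outcome.

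The trial is sized at 80% power with almost no reserve, so an unused source of precision is worth a look. At stake is the width of the confidence interval and some power, not the validity of the test.

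Two smaller matters concern the same sentence of the plan. The choice between random and fixed is left open for every stratification factor, including one with only two levels, for which a random-effect variance can hardly be estimated. And a reader of the abstract alone would not know that bypass is one of those factors.

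**Working it through.** **Inputs from the Sample size and Statistical analyses sections:** mean AUC 242 (control) and 169 (treatment), common SD 183, two-sided Student test, 80% power, 100 analysable patients per arm (105 after allowing 5% missing), two-sided 0.05.

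**Assumed input:** r, the correlation between baseline hsTnI and AUC on the analysis scale. The article gives no value, so a range is shown.

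**Step 1: reproduce the plan's figure.** Difference = 242 − 169 = 73. Standardised difference d = 73/183 = 0.399. SE of the difference = 183 × √(2/100) = 25.9. The noncentrality is 73/25.9 = 2.82 on 198 degrees of freedom, and exact t-test power is 80.2%. The exact sample size for 80% is 99.6, so 100 per arm. The plan's figure holds. It is for an unadjusted test, so it does not rely on a baseline covariate.

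**Step 2: add the covariate.** With a linear baseline term, residual SD = SD × √(1 − r²), and the SE of the treatment effect shrinks by the same factor. The degree of freedom lost is negligible here. For example, at r = 0.3 the residual SD is 183 × √0.91 = 174.6, a reduction of 5%.

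| assumed r | residual SD | SE reduced by | power at 100 per arm | n per arm for 80% |
|---|---|---|---|---|
| 0 | 183.0 | 0% | 80.2% | 100 |
| 0.1 | 182.1 | 0.5% | 80.5% | 99 |
| 0.2 | 179.3 | 2% | 81.7% | 96 |
| 0.3 | 174.6 | 5% | 83.7% | 91 |
| 0.4 | 167.7 | 8% | 86.5% | 84 |
| 0.5 | 158.5 | 13% | 90.0% | 75 |

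**Step 3: scale.** The power column uses d = 0.399, which is on the raw AUC scale. The proportional cut in SE, 1 − √(1 − r²), applies on any scale provided r is the correlation on that scale. The powers carry over to a transformed outcome only if the standardised effect there is also about 0.40. The article gives no effect or SD on another scale.

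**Step 4: which factors are in the model.** The Randomization section lists centre and need for bypass. The model takes in each variable used for stratification. Read together, they put bypass in the primary model. The abstract's shorter list does not change that.

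**The case against.** The strongest reply is that nothing here is wrong. The article condenses a longer protocol, and an analysis plan that is not shown may add covariates. The text names arm and the stratification factors but does not say that these are the only terms. Randomisation makes the comparison valid without baseline, and the type I error already allows for chance imbalance. All of this stands, and it is why the point is an improvement and not a defect.

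It is also fair that the gain may be small. Emergency surgery, acute coronary syndrome within 7 days and severe renal insufficiency are exclusion criteria. They plausibly narrow the spread of baseline hsTnI and so weaken its correlation with the AUC. At r = 0.2 the gain is 1.5 percentage points. This stands too, but a small expected gain is no reason to leave out a term that costs nothing.

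Three stronger readings are tempting, and the article supports none of them:

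- A reader might infer that the primary analysis is biased or underpowered. It is neither: Step 1 reproduces the stated power for the unadjusted test.
- A reader might infer from the abstract that bypass is left out of the model, which would make the standard error too large because randomisation is balanced on it. The Randomization section is the operative text and includes bypass, so that harm does not arise.
- A reader might infer that bypass will be fitted as a random effect. The wording permits it but does not say so; centre random and bypass fixed is the natural reading.

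One condition applies to the remedy. A covariate must not be affected by treatment. The baseline sample is taken after induction, and remote preconditioning also begins after induction; the article does not state which comes first. An early effect on troponin seems unlikely, but the order should be confirmed.

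**Conclusion.** The primary model as described is valid and meets its stated power of 80% (80.2% recomputed). It leaves unused, at least in this article, a baseline value that the protocol already collects. Prespecifying it would bring a gain in precision at no cost: about 82% to 90% power at 100 per arm if r lies between 0.2 and 0.5, and next to nothing below 0.2. That range is an assumption, and the powers rest on the plan's own standardised difference of 0.399 and on a roughly linear relation between baseline and outcome on the analysis scale. No change of sample size follows, and this point gives no ground for changing the outcome scale.

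The differing stratification lists are a real inconsistency but a clerical one. The open choice between random and fixed needs only a short clarification.

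**What to change.** In the analysis plan, before unblinding:

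- Name baseline hsTnI, suitably transformed (for example log), as a fixed covariate in the primary model, on whatever outcome scale the plan adopts. The rule that peak and 24-hour hsTnI are analysed like the main outcome then carries it to both.
- Say how a missing baseline value is handled, and confirm that the sample precedes the start of the bundle.
- List the stratification factors by name in the model: need for bypass as a fixed effect, and centre as either random or fixed, chosen in advance.

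As an editorial correction, let the abstract name both factors: centre and "individual need to perform coronary bypass during aortic valve surgery".

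The cost is a few sentences. No new data, visits or patients are needed.

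### The time-to-event option for ICU stay names hospital discharge as its event, so ICU discharge would go unanalysed under that option and hospital discharge would be analysed twice

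*Protocol article*

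**What the plan says.** The Outcomes section of the protocol article lists ICU stay and hospital stay as separate secondary outcomes: "extubation time, length of stay in ICU and hospital". Postoperative data also lists both among the items collected.

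Statistical analyses then sets the methods:

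- Ventilation and ICU stay share a sentence: "The duration of mechanical ventilation and the duration of stay in the ICU will be similarly analyzed".
- Two methods are permitted: "either after log-transformation of the values or using a survival analysis technique".
- The events for the time-to-event method are "the time to mechanical ventilation discontinuation or the time to discharge from hospital, respectively".
- The model for that method is optional: "A frailty Cox model may be used to allow for the variables used for stratification".
- Hospital stay is handled on its own: "The length of hospital stay will be analyzed with a Cox frailty model adjusted for the variables used for stratification".

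The article does not say how a patient who dies while ventilated, in the ICU or in hospital enters any of these analyses.

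**The concern.** The shared sentence has two subjects in a fixed order, ventilation and then ICU stay. Its parenthesis names two events in the same order, and *respectively* matches them one to one. The second event should therefore end the ICU stay, but the text gives the end of the hospital stay.

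A programmer who follows the text would code the wrong event for a named outcome and produce a second analysis of hospital discharge. In addition, the choice between the two methods, which should be a choice of model only, becomes a choice of endpoint: log-duration analyses ICU stay, and time-to-event analyses hospital stay. If that choice were made after the data were seen, it could change what is reported as the ICU result.

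**Working it through.** **1. What each option analyses, read literally**

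| Outcome (Outcomes section) | Log-duration option | Time-to-event option as worded |
|---|---|---|
| Ventilation duration | ventilation duration | ventilation stopped |
| ICU stay | ICU duration | discharge from hospital |
| Hospital stay | not offered | Cox frailty model for hospital stay |

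Under time-to-event, hospital discharge is analysed twice and ICU discharge never. Under log-duration, each outcome is analysed once, with hospital stay kept in its own Cox model. The mismatch lies only in the ICU row of the last column.

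**2. Does a design figure depend on it?** The only sample-size calculation is for the troponin AUC. Inputs from the Sample size section are means of 242 and 169 (difference 73), SD 183, two-sided test and 80% power; the 0.05 level is from Statistical analyses. n per arm = 2 × (1.960 + 0.842)² × (183/73)² = 2 × 7.849 × 6.284 = 98.6, so 99 against the stated 100. Power at 100 per arm is 80.2% to 80.5%. The figure reproduces and does not involve the stay outcomes.

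**3. How much could deaths matter in a log-duration model?** The article gives no mortality, time of death or median stay, so all values here are assumptions. Suppose deaths are kept at their observed duration *d*, are unrelated to the stay the patient would otherwise have had, and differ between arms by Δp. With median stay *m*, the ratio of geometric means is exp[Δp × ln(d/m)]. Take deaths on day 3 in 2% versus 5% of patients, so Δp = 0.03:

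| Assumed median | Δp × ln(d/m) | Ratio, arm with more deaths / other arm |
|---|---|---|
| 10 days | 0.03 × (−1.204) = −0.036 | 0.965 |
| 5 days | 0.03 × (−0.511) = −0.015 | 0.985 |
| 3 days | 0 | 1.000 |
| 2 days | 0.03 × 0.405 = 0.012 | 1.012 |
| 12 hours (ventilation) | 0.03 × 1.792 = 0.054 | 1.055 |

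The direction depends on whether deaths come before or after the typical discharge or extubation.

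**4. Methods compared on one assumed ICU scenario.** A large simulation used log-normal ICU stay with median 3 days and log SD 0.6, no arm effect on stay, every death before the would-be discharge, and control mortality of 2%.

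| Treated-arm mortality | Log-duration ratio | Discharge HR, censored at death | HR, death counted as end of stay | HR, deaths never discharged |
|---|---|---|---|---|
| 4% | 0.98 | 0.99 | 1.02 | 0.93 |
| 6% | 0.97 | 0.98 | 1.02 | 0.87 |
| 10% | 0.94 | 0.96 | 1.05 | 0.77 |

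A ratio below 1, or an HR for discharge above 1, would look like benefit in the treated arm. With 105 per arm, the standard error of the log ratio is about 0.6 × √(2/105) = 0.083. Even the largest shift, ln 0.943 = −0.059, is about 0.7 of a standard error.

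**The case against.** The strongest reply is that this is a drafting slip. The subject of the sentence is plainly ICU stay, the two stays are listed and collected separately, and replacing one word cures the text. That is probably how it arose. It remains a stated rule that gives the wrong event, so it should be corrected and not left to the analyst's inference.

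Three stronger readings are tempting, and the documents do not support them.

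- *A reader might infer that ICU stay is never tested.* The log-duration option analyses ICU stay itself; only the time-to-event option misses it.
- *A reader might infer that deaths will count as short stays or be censored, so that early death looks like benefit.* The article states no such rule, and an article commonly leaves that detail to the full protocol or analysis plan, so the silence is no finding. A false benefit also needs particular conditions: deaths kept as observed durations and occurring earlier than the typical discharge, or death counted as the end of the stay. Censoring at death gives a cause-specific hazard, which showed no false benefit in the scenario above. The log option is not offered for hospital stay at all.
- *A reader might infer that the separate survival analysis cannot be estimated*, since "Survival will be analyzed with a Cox model adjusted for the variables used for stratification" and deaths may be few. That rests on an assumed mortality and on entering centre as fixed terms. The chance that at least one arm has no death is 2(0.99)^105 − (0.99)^210 = 57.5% at 1% mortality but 0.9% at 5%, and the article gives no rate. It is not part of this point.

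Leaving the choice of method open would also be unremarkable in an article. It matters here only because the two options, as worded, have different endpoints.

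**Conclusion.** The point holds as a minor correction to a secondary endpoint. The event paired with ICU stay is wrong on the face of the text; this rests on the wording alone and needs no assumption. Under the time-to-event option, ICU discharge is not analysed and hospital discharge is analysed twice.

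The preference for a method that recognises death is secondary. A log-duration model cannot separate a death from a discharge, but the size and direction of any resulting bias depend on mortality and timing that the documents do not give. On the assumed values, the log-duration ratio ran from 0.94 to 1.06, which is small beside the precision available with 105 patients per arm. The primary analysis and sample size are unaffected.

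**What to change.** In Statistical analyses, change the event paired with ICU stay from hospital discharge to discharge alive from the ICU, and leave hospital discharge to the existing hospital-stay analysis.

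Before the data are examined, fix one method for ventilation and ICU stay. Time-to-event is preferable, with death as a competing event for extubation, ICU stay and hospital stay alike. Two forms would serve: keep patients who die as never reaching the event, or report the cause-specific hazard of discharge (or extubation) alongside that of death. If the full protocol or analysis plan already sets such a rule, the article's wording need only be brought into line with it.

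The cost is a few words of analysis text. Both lengths of stay, extubation time and 30-day deaths are already collected, and the Trial status section reports recruitment still open, so the change can precede analysis.
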